#### Process evaluation

Our process evaluation is informed by MRC guidance and our theory of change (Fig. 7), and captures how the intervention was implemented, fidelity to plans, reach of the intervention, pathways to impact and contextual factors that explain heterogeneity in effects. The Theory of Change was developed through two workshops and refined after reviewing formative research findings. It details the hypothesised mechanisms which will enable change in our primary and secondary outcomes in intervention areas and the assumptions that underpin them.

**Fig. 7 Fig7:**
[figure not shown]
Theory of change

Quantitative process outcomes, captured through surveillance questionnaires, have been included in Table 2. We explore how the context in both intervention and control areas may influence intervention effect [109]. We will describe the implementation of the intervention and fidelity to plans through analysis of process monitoring forms administered by supervisors of NAs. A senior process evaluation officer will review these data, and conduct focus group discussions with supervisors and NAs three times during through the intervention to explore how context affected the implementation of the intervention, and to analyse factors affecting attendance at groups and exposure to home visits. If we find effects on our primary outcome, we will use mediation analyses to unpack pathways along our theory of change, exploring whether effects are explained by changes in health literacy, social norms, dietary iron intakes, other micronutrient intakes, IFA compliance or deworming.

#### Economic evaluation

Cost and cost-effectiveness of the intervention will be estimated from a provider perspective. The costs of design and implementing the intervention package (programme costs) and costs to public health care providers will be estimated. Programme cost data will be collected from the project accounts of the implementing partner, staff time use surveys and interviews with project staff. Costs to public health care providers as a result of any increased demand for health services caused by the intervention, will be estimated using health seeking data from the 30 ± 2-week questionnaires with the study participants and available secondary data on unit costs for the services in question. Incremental cost-effectiveness of the intervention package will be calculated as compared to routine care. Incremental cost-effectiveness ratios (ICERs) will be estimated for the primary outcome and for associated disability-adjusted life years (DALYs) averted. A series of sensitivity analyses will be conducted to check the robustness of the results.

### Interim analyses {21b}

No interim analyses of intervention effectiveness are planned. Interim reports for the Data Monitoring Committee (DMC) and Trial Steering Committee (TSC) regarding recruitment, follow-up and baseline characteristics will be prepared and interim safety reports (morbidity and side effects) for the DMC.

We do not specify a formal stopping rule since the interventions under test are simply adapting WHO and government policies for IFA supplementation that are already in use. So, whilst women may consume more IFA tablets as a result of the intervention, there is no new drug being tested. The risk during the finger prick test for Hemocue testing to know the haemoglobin status is low. We also do not intend to consider modification or early stopping of the trial on the basis of interim evidence of intervention effectiveness (or lack of effectiveness). Nevertheless, the DMC is presented with harms data (adverse events and levels of morbidity) disaggregated by study arm at each meeting and could recommend to the Trial Steering Committee modification or termination of the trial.

### Methods for additional analyses (e.g. subgroup analyses) {20b}

Subgroup analyses will compare the intervention effect on the primary outcome by socioeconomic status, BMI category at enrolment and by baseline anaemia status (Table 4). The intervention effect is presented within subgroups and testing for differential effect by subgroup is based on an interaction term, using the same regression approach as for our main analyses.

Our main analyses are under the intention-to-treat principle, i.e. as randomised at the cluster level regardless of uptake of home visits, tailored IFA dosage or PLA. However, for the primary outcome, we will also conduct a ‘per protocol’ analysis in which participants who received the intervention only (i.e. who had PLA groups running in their community and received at least one home visit) are compared to all participants in the control arm.

Within the intervention arm, we will analyse the dose-response effect upon the primary outcome (Table 4). Three separate exposure scores will be derived based on the (1) number of home visits received, and number of family members engaged during visits, (2) number of PLA meetings attended by PW and number attended by family members and (3) number of IFA consumed. We will investigate the association between each score and the primary outcome, with and without adjustment for the other scores.

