##### Anaemia screening and tailored iron-folic acid therapy

At each home visit, following the nutrition counselling, the NA will measure the PW’s haemoglobin concentration using a hand-held Hemocue Hb 301+ analyser, measure her mid-upper arm circumference (MUAC) with a SECA tape (93/42/EEC) to assess thinness, and explain the results. Following GoN guidelines, the NA will advise the PW to take IFA as follows:
Not anaemic (Hb ≥ =11 g/dL), one IFA tablet (60 mg elemental iron and 400 μg folic acid) per day.Mildly or moderately anaemic (Hb 7–10.9 g/dL), two IFA tablets (120 mg elemental iron and 800 μg folic acid) per day.Severely anaemic (Hb < 7 g/dL), the NA will immediately refer the PW for a blood transfusion at a higher health facility.

At visit 1 (at 12 to 21 weeks’ gestation), the NA will provide sufficient IFA tablets for a period of 4–10 weeks until her second visit, at 22 to 26 weeks’ gestation. For all women, NAs will emphasise the importance of increasing dietary diversity and consuming micronutrient-rich food. For women with low (< 230 mm) or very low (< 210 mm) MUAC, the NA will also emphasise the importance of consuming additional calories through more frequent and/or larger meals and taking adequate rest. For women with MUAC ≥ 300 mm, the NA will stress the importance of keeping active during pregnancy and avoiding sugary or fatty foods and large portions of rice.

After repeating the haemoglobin and MUAC measurements at the second visit, the NA will explain to the woman how her anaemia and thinness status have changed and provide the appropriate IFA dose. She will also assess compliance to IFA by asking the PW about their tablet consumption and checking used blister packs. At visit 2, the NA will provide a single (400 mg) albendazole tablet if the PW has not already received it as per Nepal’s national protocol for women in their second trimester.

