**IFA and ANC processes**	
Numbers of IFA tablets consumed in relation to those prescribed	
Uptake of any antenatal care	
Quality of antenatal care	
Gestational age at first ANC visit	

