**Main exposure (independent) variable for analyses of outcomes above:**	
Study arm: Home visiting +PLA versus Control (which is the reference group)	
**Within the intervention arm the levels of exposure to PLA women’s groups and home visits are coded in three (independent) variables for analyses of a dose-response effect upon the outcomes above (or a subset of them):**	
Exposure to women’s group—score of exposure constructed out of number of meetings attended by pregnant woman and number attended by family members	
Exposure to home visiting with tailored counselling and dose of iron-folic acid supplements—score of exposure constructed out of number of meetings attended by pregnant woman and number attended by family members	
IFA consumption during pregnancy (count or ordinal score constructed from the count)	

Our primary analysis will also adjust for haemoglobin at enrolment, to gain precision, but we acknowledge the trade-off that this may dilute intervention effects since in principle cluster-level intervention effects could be mediated through haemoglobin at enrolment. In a sensitivity analysis, we will remove adjustment for haemoglobin at enrolment.

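### The IFA tablet-count dose-response analysis is confounded by indication: low Hb doubles the prescribed tablets, so the slope is biased downward and may reverse sign

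*Protocol article*

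**What the plan says.** The Objectives {7} list a dose-response analysis of exposure to PLA groups, home visits and number of IFA consumed. Methods for additional analyses {20b} sets it up: "Within the intervention arm, we will analyse the dose-response effect upon the primary outcome (Table 4"). It names three scores, the last being "and (3) number of IFA consumed". Table 4 codes that exposure as "IFA consumption during pregnancy (count or ordinal score constructed from the count"). The adjustment named for these models is mutual: "We will investigate the association between each score and the primary outcome, with and without adjustment for the other scores".

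The intervention description (Anaemia screening and tailored iron-folic acid therapy) ties the daily number of tablets to the Hb measured at each home visit. Women who are not anaemic are advised to take "one IFA tablet (60 mg elemental iron and" folic acid) per day. The next category reads "Mildly or moderately anaemic (Hb 7–10.9 g/dL), two IFA tablets" per day. The visits fall at 12–21 and 22–26 weeks.

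Enrolment Hb is in the Table 4 covariate list, marked for the primary outcome analysis. No covariate list contains the home-visit Hb or the prescribed dose. Table 2 does include "Numbers of IFA tablets consumed in relation to those prescribed", and the dose prescribed, but only as process indicators.

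**The concern.** The reason a woman is told to take more tablets is low Hb in mid-pregnancy, and Hb tracks over the following weeks into the outcome. A raw count mixes three things: adherence, weeks of follow-up since the first visit, and how anaemic the woman was. The third pulls the slope down whatever iron does. An ordinal score built from the count inherits the same problem, and the PLA and home-visit scores do not carry the reason for the doubled dose.

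The protocol presents this as an analysis of the effect of different levels of exposure, and says the findings will inform government policy on IFA adherence. A null or negative tablet slope could be misread as iron not working, or as the home-visit and PLA components doing the work instead.

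Two smaller matters sit in the same section. Table 4 defines the home-visit score by meetings attended, repeating the women's-group wording, while {20b} defines it by visits received and family members engaged. And the per-protocol analysis selects in one arm only: women who "received at least one home visit) are compared to all participants in the control arm".

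**Working it through.** **1. Inputs from the protocol.** 421 women with an outcome per arm, 27 clusters per arm, SD 1.2 g/dL, ICC 0.09, CV of cluster size 0.27 (Sample size {14}); dose rule and visit windows as above; anaemia prevalence 27%, 44% or 52% (Background; Study setting).

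The protocol gives no figure for the dose-response analysis, so the primary power figure serves to check these inputs. Design effect = 1 + ((CV² + 1)m − 1) × ICC = 1 + (1.0729 × 15.6 − 1) × 0.09 = 2.416. Effective n per arm = 421 / 2.416 = 174.2. Standard error = 1.2 × √(2/174.2) = 0.1286. 0.4 / 0.1286 − 1.96 = 1.15, giving power 87.5% against 88.3% stated. The other three Table 3 entries give 84.8, 81.5 and 78.3% against 85.7, 82.1 and 79.0%. The inputs are sound.

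**2. What the count measures.** From visit 1 (12–21 weeks) to 30 weeks is (30 − 21) × 7 = 63 to (30 − 12) × 7 = 126 days. Full adherence gives 63–126 tablets to a woman never anaemic and 126–252 to one anaemic throughout. Over the same number of days, an anaemic woman taking half her tablets has the same count as a fully adherent non-anaemic woman.

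**3. Size and direction.** One intervention arm was simulated (200 runs per scenario), with one or two tablets a day set by Hb below 11 at each visit, and outcome Hb regressed on tablets by ordinary least squares. Assumptions not in the protocol: correlation of enrolment and outcome Hb 0.3–0.7; adherence mean 0.8 (SD 0.1) or 0.6 (SD 0.25), unrelated to Hb; tablets counted from visit 1; no cluster random effect in the fitted model; no measurement error. Entries are ranges of the mean slope in g/dL per 100 tablets, with the share of runs significantly negative.

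| True effect | No Hb adjustment | Enrolment Hb added |
|---|---|---|
| 0 | −0.66 to −1.60 (about 100%) | −0.29 to −0.95 (89–100%) |
| +0.2 | −0.48 to −1.42 (98–100%) | −0.10 to −0.76 (17–100%) |
| +0.4 | −0.29 to −1.27 (68–100%) | −0.56 to +0.09 (0–99%) |
| +0.8 | −0.96 to +0.09 (0–100%) | −0.21 to +0.48 (0–28%) |

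Subtracting the true effect gives the bias. With enrolment Hb it is −0.29 to −0.95 (true 0), −0.30 to −0.96 (+0.2), −0.31 to −0.96 (+0.4) and −0.32 to −1.01 (+0.8), so about −0.3 to −1.0 throughout. Without Hb adjustment it is about −0.7 to −1.8. Further runs with visit and outcome dates drawn from the protocol's windows and gestational age added (for example correlation 0.4–0.6, adherence mean 0.6–0.7) gave about −0.3 to −0.6 with no true effect and −0.24 to +0.07 with a true +0.4, inside the wider ranges above.

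**4. The alternative exposure.** With tablets consumed divided by tablets prescribed, adjusted for enrolment Hb, the slope from none to all tablets taken is −0.02 to +0.04 with no effect, +0.20 to +0.31 (true +0.2), +0.43 to +0.58 (true +0.4) and +0.87 to +1.11 (true +0.8).

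This holds if adherence is unrelated to dose. If women on two tablets take a 20% smaller share, the ratio adjusted for enrolment and visit-1 Hb shows a spurious benefit of about +0.10 to +0.32 with no true effect. Adding the prescribed dose at both visits brought the slope back to about zero in a further check.

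Keeping the count and adding Hb at both visits also removes the bias under no effect, but gives only +0.08 to +0.22 for a true +0.4, because visit-2 Hb lies on the causal path.

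**The case against.** The strongest reply is that {20b} describes mutual adjustment of the three scores and does not exclude other covariates. Outcome measurement in the third trimester says gestational age at measurement is adjusted for in all analyses. Table 4 lists enrolment Hb for the primary outcome, which is the dose-response outcome. The missing-data section {20c} says enrolment measures are covariates in the regression models, and {20a} leaves covariate adjustment to the SAP. {20b} also speaks of an association. This stands as far as it goes: the unadjusted column above may not be the model that is fitted. It does not dispose of the point. The exposure is fixed as a count in the Objectives, Table 4 and {20b}, and the second column shows that enrolment Hb leaves a downward bias, because the dose is set on later readings.

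A reader might infer that the analysis will show iron lowering Hb. The documents do not support that certainty. The sign depends on the true effect, the spread in adherence, how closely Hb tracks and whether enrolment Hb is in the model; with a strong effect and varied adherence the slope can be near zero or positive. Visit timing and IFA from routine sources also move the count for reasons other than Hb.

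The ratio is not a complete cure either. The section on modifying interventions {11b} foresees that the higher dose may not be tolerated, so adherence may differ by dose. Unvisited women have no prescribed denominator.

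On the per-protocol comparison, it supplements intention-to-treat, and any size put on its bias would rest on an unvisited share and an Hb gap that the protocol does not give. Using study arm as an instrument for receiving a visit would not rescue it, because PLA groups can reach unvisited women directly.

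**Conclusion.** The concern holds as one of confounding by indication. As written, the within-arm association between tablet count and Hb is biased downward and may be null or reversed even if iron helps. Under the stated assumptions the bias is about −0.3 to −1.0 g/dL per 100 tablets with enrolment Hb in the model, and about −0.7 to −1.8 without it. These figures are illustrative, since adherence and Hb tracking are assumed; the direction follows from the dose rule. The intention-to-treat comparison, the primary outcome and the power are untouched. This should be fixed before analysis. The Table 4 wording and the one-sided per-protocol set are minor.

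**What to change.** Replace exposure (3) by tablets consumed relative to tablets prescribed, counting the dose actually advised, including any reduction. Adjust for, or stratify by, the prescribed dose at each visit, and adjust for enrolment Hb, the visit-1 Hb recorded by the nutrition assistant, and gestational age at measurement. Because the visit-2 dose depends on an Hb that earlier tablets may have raised, note that adjusting for it may somewhat dilute a real effect; a marginal structural model is an option if the team wants to handle this formally. State that the analysis covers women with at least one home visit, is observational, and that adherence may differ by dose.

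Reconcile the Table 4 home-visit score with {20b}. Report the per-protocol comparison as non-randomised, adjusted or weighted on enrolment covariates.

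The cost is wording in the protocol and SAP and a little extra analysis. Prescribed dose, consumption relative to prescription, and visit Hb are already recorded. The one loss is that unvisited women drop out of this score.

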### Methods in analysis to handle protocol non-adherence and any statistical methods to handle missing data {20c}

We expect very low missing data in our baseline covariates and in the haemoglobin measure at enrolment. We do anticipate some women will not have a primary outcome value. Where this is due to miscarriage, we do not regard this as ‘missing’, but where the woman is unavailable or has moved away, we consider this to be missing. We do not however consider that imputation of the primary outcome is helpful since there is little information on which to base the imputation other than baseline/enrolment measures, which we are including as covariates in our regression models.

### Plans to give access to the full protocol, participant-level data and statistical code {31c}

Two versions of the trial protocol are publicly available, a version published on the ISRCTN registration page, and this published protocol.

Participant-level data will be shared only at the time of the publication of the main trial paper but will be made fully available subsequently. Statistical code for conducting the trial analysis will be shared in a web annex to the main trial paper.

## Oversight and monitoring

### Composition of the coordinating centre and trial steering committee {5d}

The coordinating centre for the trial is the Trial Management Group comprised of senior representatives from HERD International, the PI / local PI from UCL, the trial statistician and key personnel involved in the day-to-day management of activities on the ground. The TMG meet weekly during trial set-up period and two-weekly at other times.

The Trial Steering Committee is comprised of experts from various institutions in Nepal, the UK, India and Canada who are specialists on maternal nutrition, anaemia, haematology, conduct of trials and/or maternal nutrition in Nepal. The role of the TSC is to provide oversight for the trial, providing advice through its independent Chair to the Trial Management Group (TMG), MRC and/or any other Funder on all aspects of the trial. The TSC will meet at least yearly, but interim meetings will be organised as required, in person or by teleconference (or by a combination of the two). Certain trial issues may need to be dealt with between meetings, by phone or by email. Full details of the TSC charter and membership are provided in Supplementary Annex 1.

### Composition of the data monitoring committee, its role and reporting structure {21a}

The data monitoring committee is made up of experts from the fields of global health trials, statistics, obstetric haematology, maternal nutrition, micronutrient status and research ethics in Nepal, with three members from Nepal and the remaining three from the USA, UK and India. The role of the DMC is (i) to protect and serve the CAPPT trial participants and to assist and advise the Principal Investigators so as to protect the validity and credibility of the trial; (ii) to safeguard the interests of the trial participants, assess the safety and efficacy of the interventions during the trial and monitor the overall conduct of the trial. The DMC is entirely independent of the sponsor and all members declare that they have no competing interests.

Meetings involve members and investigators who are outside Nepal joining by video link so as to reduce costs and carbon emissions. The DMC meets once to review and approve the protocol and once towards the end of the trial to review trial findings. Further interim meetings may be called if needed and the investigators may seek advice from the chair by email if the situation requires. After each meeting, the DMC chair will prepare a brief report of DMC recommendations which is signed and dated and shared with the TSC chair, the Trial Statistician and the co-PIs within 3 weeks of the meeting. The charter of the Data Monitoring Committee is provided in Supplementary Annex 8.

### Adverse event reporting and harms {22}

Surveillance questionnaires and questions posed during counselling sessions will assess side effects of taking IFA which we expect will mostly be mild symptoms including dark stool, nausea, bloating, abdominal discomfort, heartburn, loss of appetite, metallic taste and constipation. The most serious problems that could arise may be a severe allergic reaction to IFA (though this is very rare) or participants contracting COVID-19 after interacting with a trial team member. In addition, our primary outcome questionnaire will record recalled symptoms of illness including pre-eclampsia, vaginal bleeding, dysentery, gestational diabetes and malaria, though none of these are expected to be associated with our intervention.

Although we do not expect any adverse effects of attending a PLA group, of being visited for counselling or interviews/measurements, we will establish a complaints procedure and ensure that trial participants and their families know who to call or where to visit to register a complaint. Contact details are provided in the participation information sheet, and participants will be reminded of the complaints procedure at each visit.

If any unanticipated effects (including maternal deaths or COVID-19 cases associated with trial participation) are noted by the NAs, interviewers or dietary data collectors, they will inform field coordinators / managers who will telephone and/or visit the home of the respondent to ascertain the extent and nature of the problem and complete an adverse events form. Investigators will then classify each event as a minor adverse reaction (MAR), severe adverse reaction (SAR), severe adverse event (SAE) or suspected unexpected serious adverse reaction (SUSAR). These will be presented to PIs and to the Data Monitoring Committee where appropriate. In the case of illness, all participants are referred to the appropriate referral centre depending on the severity of their condition.

